### Measures

#### Cognitive target

We anticipate that the MemFlex programme will improve, and maintain improvement in, memory flexibility relative to psychoeducation. We will therefore administer the Autobiographical Memory Test with Alternating Instructions (AMT-AI^8^) at all assessments. The AMT-AI requires individuals to recall either specific or general memories in response to neutral, positive and negative cue words. Participants are asked to retrieve specific memories to a block of six cue words, general memories for a block of six cues and finally a block of 12 cues in which the individual must alternate between retrieval of specific and general memories. The cues are randomised to blocks, and the order in which the blocks are presented is also randomised. The main outcomes are the number and proportion of correct responses for each block (ie, specific, general, alternating).

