#### Statistical analysis plan

The trial statistician is blind to study objectives, and will complete all analyses in accordance with CONSORT standards. No interim analyses are planned during data collection. Between-group difference on our primary clinical outcome of number of depression-free days will be analysed using an independent samples t-test, or analysis of covariance if necessary to account for any baseline differences. Time to depressive relapse will be compared between groups using Cox regression survival analysis. Analysis of our cognitive target variable, secondary clinical outcomes and additional process measures will be analysed using analysis of variance (ANOVA) with time (pre, post, 6 and 12 follow-up) as a within-subjects factor, and condition (MemFlex, psychoeducation) as a between subjects factor. Any baseline differences in the cognitive target, symptom severity on the BDI-II, concurrent treatment or demographics will be covaried in analyses. Diagnostic status at 12-month follow-up will analysed using logistic regression. Residual depression symptoms and number of previous episodes (as an index of depression severity), and score on the AMT-AI (as an index of bias severity) at preintervention will be explored as moderators of treatment efficacy by computing product variables that will be analysed using linear regression. Finally, we will explore mechanisms of change by determining whether intervention effects are mediated by change on the AMT-AI and the other process measures. Indirect effects will be analysed using bootstrapped samples in the Process statistical package. Intent-to-treat analysis will be used for those lost to attrition by using multiple imputation to account for missing data. The number of imputed datasets will approximate the percentage of missing data.^46^ Any exploratory, per-protocol analyses will use data from participants who have completed six out of the eight workbook sessions. Exploratory ANOVAs will also be completed to explore between-group difference in pre-to-post intervention change on the separate AMT-AI blocks, to determine whether MemFlex may have a larger impact on specific, categoric or alternating recall.

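### The plan asks on which type of recall MemFlex has the larger effect, but the separate-block ANOVAs it names do not test a difference between blocks

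*Protocol article*

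**What the plan says.** All AMT-AI analyses are described in the Statistical analysis plan section of the protocol article.

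- **Main analysis of the cognitive target.** This is an ANOVA "with time (pre, post, 6 and 12 follow-up) as a within-subjects factor, and condition (MemFlex, psychoeducation) as a between subjects factor". Block is not a factor.
- **Block question.** The last sentence of the section adds exploratory ANOVAs "to explore between-group difference in pre-to-post intervention change on the separate AMT-AI blocks". Their purpose is "to determine whether MemFlex may have a larger impact on specific, categoric or alternating recall". I take categoric recall to be the general block.

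The Cognitive target section defines the blocks. The specific and the general block use six cues each. The remaining one is described as "finally a block of 12 cues in which the individual must alternate between retrieval of specific and general memories". Each block is scored both as a number and as a proportion correct.

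The article gives no significance level for the block analysis, and no rule for deciding that the effect is larger in one block than in another.

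**The concern.** The question is whether the condition effect differs between blocks, so its null hypothesis is that the three effects are equal. An ANOVA of change within one block has a different null: that the condition effect in that block is zero. Three such analyses can show which blocks have a detectable effect. They cannot show that one effect exceeds another, because a significant block beside a non-significant one is compatible with equal effects.

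Both the question and the method are stated in one sentence, and the method does not answer the question. At stake is how the trial describes the profile of recall change after MemFlex: a uniform benefit could be read as selective.

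**Working it through.** **Inputs from the protocol article**

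- Three blocks of 6, 6 and 12 cues (Cognitive target).
- 25 per condition wanted, 35 per condition recruited, up to 25% attrition (Power analysis).
- d=0.48 for overgeneral memory (Introduction). This is a pre-to-post effect from an uncontrolled pilot, so it serves only as an anchor.

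**Assumptions not in the article**

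Normal change scores with equal variances, two-sided alpha 0.05, the same true between-group effect d in every block, and a between-block correlation rho of the change scores.

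**Step 1: the plan's own figure.** 25/(1 − 0.25) = 33.3, rounded up to 34. The stated 35 is consistent with this, and 35 × 0.75 = 26.25 would remain. The range 25 to 35 per arm therefore covers full loss to full retention.

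**Step 2: power in one block** (normal approximation).

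| d | 25 per arm | 35 per arm |
|---|---|---|
| 0.3 | 18.4% | 24.0% |
| 0.48 | 39.6% | 51.9% |
| 0.5 | 42.4% | 55.2% |
| 0.8 | 80.7% | 91.7% |

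**Step 3: closed form at rho=0.** With power p in each of three independent blocks, the chance that one or two of three are significant is 1 − p³ − (1 − p)³ = 3p(1 − p). At d=0.5:

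- 25 per arm: 3 × 0.424 × 0.576 = 0.733.
- 35 per arm: 3 × 0.552 × 0.448 = 0.742.

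Power near one half is where blocks disagree most by chance.

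**Step 4: simulation with correlated blocks** (8,000 trials per setting). The table gives the percentage of trials with a mixed pattern when the true effect is equal in all blocks.

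| d | n per arm | rho=0 | 0.3 | 0.5 | 0.7 |
|---|---|---|---|---|---|
| 0.3 | 25 | 45.1 | 37.7 | 32.9 | 25.5 |
| 0.3 | 35 | 54.0 | 45.3 | 38.4 | 29.9 |
| 0.5 | 25 | 72.9 | 58.6 | 49.0 | 37.0 |
| 0.5 | 35 | 74.1 | 60.2 | 50.4 | 38.6 |
| 0.8 | 25 | 49.4 | 42.9 | 35.5 | 27.1 |
| 0.8 | 35 | 24.7 | 22.3 | 18.5 | 14.9 |

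The rho=0 column agrees with Step 3. Repeat runs differ by about one percentage point. At rho=0.9 the rates fall to 20.3% and 21.7% for d=0.5, and to 8.9% for d=0.8 with 35 per arm.

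**Step 5: the direct test.** One condition by block test on the change scores (Hotelling T² on two block contrasts) rejected in 4.6% to 5.5% of trials across all settings with equal effects.

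**Step 6: scale.** With fixed cue counts, number correct equals proportion correct times 6 or 12. Within one block this multiplies every score by the same constant, so F and p do not change. Across blocks it matters: an equal gain of 0.10 in proportion is 0.6, 0.6 and 1.2 cues. With an assumed SD of 0.2 and rho=0.3, the condition by block test rejects in 5.1% on the proportion scale. On the number scale it rejects in 11.4% (25 per arm) and 15.3% (35 per arm).

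**The case against.** The strongest reply is that the analysis is labelled exploratory and the trial's declared purpose is estimation. The article does not say that a mixed pattern of significance will be taken as proof of a difference; a comparison of block-wise effect sizes is equally open to the authors. This stands as a limit on the rates above: they are the chance of a mixed pattern, and become error rates only under a significance-based reading. It does not close the gap, since comparing estimates by eye gives no measure of uncertainty for the difference.

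A second reply is that a condensed article leaves such detail to the full plan. That would hold if the article were silent, but it names a method, and that method does not address the stated aim.

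Three stronger readings are tempting and are not supported:

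- **The unequal cue counts push the planned tests towards the alternating block.** Through the choice of scale they cannot (Step 6). The longer block might also be measured more precisely, but the article gives no SDs. That block adds a switching demand, so its SD could be larger or smaller.
- **The trial's aim of exploring mechanisms rests on this analysis.** In the Statistical analysis plan section, that aim is attached to the mediation analysis.
- **A false selective finding would reshape the workbook or the later trial's cognitive target.** The article says the later trial will draw on effect sizes for the primary clinical outcomes. Nothing ties block results to such decisions.

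**Conclusion.** The point holds in limited form: the planned separate-block ANOVAs do not test whether the MemFlex effect is larger in one block than another. If blocks are compared by significance at two-sided 0.05, equal effects of d=0.5 give a mixed pattern in about 37% to 74% of trials, and equal effects of d=0.3 in about 25% to 54%, for 25 to 35 per arm and rho from 0 to 0.7. The direct test errs in about 5%. The effect against an active control, the correlation and the decision rule are all assumed. The problem shrinks with very high correlation, or with a large effect and full retention. No primary or secondary clinical outcome is touched; what is affected is one exploratory interpretation.

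**What to change.** For this exploratory question, replace the separate-block ANOVAs as the test of larger impact with one mixed ANOVA or mixed model of pre-to-post change in proportion correct. Use block (specific, general, alternating) as the within-subjects factor and condition as the between-subjects factor. Base any statement that one type of recall is affected more on the condition by block interaction and its pairwise contrasts with 95% CIs. Keep the block-specific effects as descriptive estimates with CIs. Specify proportion correct, because the combined model would otherwise mix blocks of 6 and 12 cues.

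The cost is one sentence of wording and no new data. The downside is precision. For an effect of d=0.8 confined to one block, the interaction test has 66% to 82% power at 25 per arm and 82% to 93% at 35 (rho 0.3 to 0.5). For d=0.8 in one block and 0.2 in the others, power is only 41% to 71% across both sizes. A non-significant interaction should therefore not be reported as evidence of equal effects.

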### Trial management

The trial management committee will be formed by TD, CH and trial statistician (PW). The trial coordinator (CH) will complete data checks to ensure data quality.

### Ethics and dissemination

All individuals will provide informed consent prior to participation, and Medical Research Council, National Health Service and professional ethical guidelines will be adhered to throughout the study. Any necessary amendments to this protocol will be published in the trial manuscript. No restrictions have been placed on the publication of results. In addition to publication of the trial paper, results will be shared in written form to trial participants, and through seminars to clinicians and the general public.

### Safety aspects

In the unlikely occurrence of adverse events, the Medical Research Council’s structured risk assessment protocols will be used to manage risk. All risk issues will be managed by the trial coordinator (CH), in consultation with TD, both of whom are clinical psychologists experienced in treatment of depression. Any adverse events will be reported to the research ethics committee, and will be reported in the trial manuscript.

### Confidentiality and access to data

Only the trial coordinator and trial statistician will have access to the final dataset. Data will be securely stored in de-identified form on-site, and in encrypted electronic format. Personally identifiable information will be stored separately to the trial data, and will only be accessible via a dedicated access server. Once the data have been analysed and the trial is published, the final dataset will be deposited in de-identified form into the research unit’s online data repository, along with the used statistical code.

### Trial registration

The trial protocol was registered online on 25 November 2015 at ClinicalTrials.gov (identifier NCT02614326), with recruitment planned to open in January 2016. The first participant was recruited on 18 January 2016.

## Discussion

Major depression is predicted to be the largest global burden of disease by 2030.^47^ Reducing the recurrence of depression will therefore be a key issue for the coming years. This study will estimate the effect of a novel intervention, MemFlex, which aims to reduce negative and overgeneral memory biases, and thereby risk of depressive relapse. In simultaneously targeting these factors, the programme may reduce both direct and compounded effects on depressive relapse. This trial aims to estimate the range of likely effects of MemFlex, to provide a platform for a later-stage, fully powered trial, and to begin to explore mechanisms of change. If effective, MemFlex may hold promise as a low-cost and low-intensity option for reducing depressive relapse as the self-guided, workbook format of the programme would be simple and cost-effective to provide to individuals on discharge from a treatment service, or potentially as an adjunct to complex interventions such as cognitive-behavioural therapy. As the pressure that depression places on healthcare systems is expected to increase,^48^ further development of low-cost relapse prevention programmes will be vital in improving access to psychological services and quality of life for those experiencing chronic and recurrent depression.
